#### **7.5.1.5 Routine antenatal care and treatment of illness**

Routine antenatal care and treatment of any illness identified at this visit will be provided as described in section 7.3.3.1, Routine care and permitted concomitant medication, page 30. This will include the provision of an ITN if the woman does not already have one, and advice on sleeping under the net for the entire duration of the pregnancy.

#### **7.5.1.6 Recording of morbidity and medication taken**

All participants will be asked about any symptoms or illnesses they have had in the last month, and any medication taken. These will be recorded in the adverse events section of the CRF. All AEs shall also be evaluated for seriousness and reported accordingly.

### **7.5.2 Interim monthly scheduled visits**

Subsequent clinic visits will be scheduled monthly after the first visit.

#### **7.5.2.1 Serial ultrasound scans**

In selected sites, approximately 1,464 women shall be requested to undergo two more additional ultrasound scans at interim monthly visits at the approximate gestational ages of 25-28 weeks and 32-35 weeks (or otherwise at the nearest scheduled monthly visit).

#### **7.5.2.2 Biological samples**

A venous (up to 10 mL) or finger prick whole blood sample (~250 µL) will be taken for the same assays as the baseline sample, with the exception of syphilis testing which will only be conducted once at the initial visit. A second HIV test and nutritional biomarkers will be done once in third trimester only during one of the last scheduled visits prior to delivery. The samples taken for malaria diagnostics, including malaria smears will be taken for later diagnostic analysis and not for patient care. A standard malaria RDT will be taken from women with fever or a history of fever in the last 48 hours for patient care (see 7.3.2.1, Symptomatic malaria, page 29).

At each scheduled visit, the subgroup of 160 women enrolled in the nested cardiac monitoring study will have an additional 4mL of whole blood drawn for the assessment of drug levels, full blood count, and biochemistry for electrolytes, liver and renal function tests; This includes 2 mL taken just before the first dose of each course and 2 mL 4-6 hours after the 3rd dose of each course; i.e. just after the respective ECGs have been taken at these time points.

In the subgroup taken part in the micro-biota component in selected sites, the women will be requested to provide a further high vaginal swab and a stool sample for reproductive tract and gut microbiota colonisation respectively during one of the last scheduled visits prior to delivery.

Similarly, a nasopharyngeal swab will be requested again from the women taking part in the component that assesses the carriage rate of macrolide resistant *Streptococcus* during one of the last scheduled visits prior to delivery.

#### **7.5.2.3 Study intervention**

The IPTp will be administered to asymptomatic women at these visits as described in section 7.3.1, Trial Medications and interventions, page 27. If women have symptomatic malaria they will be treated as described in section 7.3.2.1.: Symptomatic malaria.

#### **7.5.2.4 Routine antenatal care and treatment of illness**

Routine antenatal care and treatment of any illness identified at this visit will be provided as described in section 7.3.2.1, Symptomatic malaria, page 29.

#### **7.5.2.5 Recording of morbidity and medication**

Participants will be asked about any symptoms or illnesses they have had since the start of pregnancy, and any medication taken, and these will be appropriately documented in the CRFs.

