| 
Visit 1: Pre-screening interview, Screening, Consent, Enrolment, Randomisation, and Allocation. First IPTp treatment dose given under direct observation.
 
Visits 2 to 4: Monthly IPTp treatment and ANC follow-up visits.
 
Visit 5: Delivery visit. To be conducted as soon as possible after birth without interrupting the initiation of breastfeeding or any necessary care required to the mother or newborn. A surface examination shall be conducted to assess for external congenital abnormalities.
 
Visits 6 and 7: Routine postnatal care, physical examination and follow-up of the mother-newborn pair.
 
a. Visits spaced approximately one month apart. The max. number of scheduled visits depends on the gestational age at enrolment (estimated median of 3 to 5).
 
b. Pre-study screening can take place any time women start visiting the ANC; i.e. even prior to 16 weeks gestation, but the intervention can only start at 16 weeks.
 
c. Cardiac safety monitoring; One ECG prior to 1st dose of each course and one 4-6 hours after the 3rd dose of each course (subgroup 160 women, 80 in each DP arm).
 
d. The first dose (day-0) always given under direct observation and subsequent 2 doses are to be taken at home (day-1 and day-2).
 
e. Baseline ultra sound scans in all women to assess the gestational age. Additional ultrasound scans to determine foetal growth at scheduled visits occurring at the approximate gestational ages of 25-28 weeks and 32-35 weeks (subgroup only), or otherwise at the nearest scheduled monthly visit.
 
f. Vomiting and other adverse events (AEs) occurring within 30 minutes of the first dose will be assessed. Subsequent AEs will be captured though passive surveillance. Participants will be encouraged to report to the study clinic for any subsequent AEs that may arise after each study visit at any time before the next study visit.
 
g. Enrolment & delivery blood sample by venepuncture (VP) (up to 10 mL) or finger prick (~250µL): All women all sites: haemoglobin level, HIV test (unless known to be HIV+), syphilis, malaria smear, dried blood spots (DBS) for molecular malaria diagnostics (not for point of care, DBS for multi-pathogen antibody assays and drug resistance. Sub-group (venepuncture): Nutritional biomarker including leptin, adiponectin, aflatoxin-albumin adduct (AF-alb) levels; antibody and cell mediated immune responses to malaria and other pathogens; biomarkers of placental function, inflammation and gestational age; malaria diagnostics, and drug levels. Remaining red cell pellets will be stored.
 
h. Interim study visits blood sample by venepuncture (up to 10 mL) or finger prick (~250µL): Same assays as for baseline, with the exception of syphilis. HIV testing and nutritional biomarkers will be done once in third trimester only during one of the last scheduled visits prior to delivery.
 
i. Umbilical cord blood (CB) sample (7 mL in subgroup and 5 mL in all others): Haemoglobin level, malaria molecular diagnostics, antibody and cell mediated immune responses to malaria and other pathogens, and nutritional biomarkers including leptin, adiponectin and drug levels. Heel prick (HP) sample (~ 500 microl) in all babies with fever or other symptoms for malaria RDT, microscopy and dried blood spot, and in subgroup of asymptomatic infants for immunological assays.
 
j. Venepuncture 2 ml blood sample taken 4-6 hours after last dose of each course (cMax) for biochemistry and drug levels (subgroup of 160 women in ECG component)
 
k. Stool sample at enrolment and last scheduled antenatal ANC visit prior to delivery in subgroup (n~1,464). Postnatally, only new-born stool sample shall be collected.
 
l. Placental samples at delivery/termination of pregnancy: placental section for histopathology, amnion roll, placental impression smear, maternal placental blood for malaria diagnostics (not for point of care), drug levels, and cord blood (i.e. newborn's side) (see cord blood sample).
 
m. Maternal anthropometric measurements: Enrolment: height; All visits: Weight, and MUAC. Sub-group only: delivery, 1 and 6-8 postpartum: skinfold thicknesses (SFTs), hip and waist circumference, bioelectrical impedance analysis and deuterium analysis (FTIR).
 |   |   |                |

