### 9.3.2.2 Secondary endpoints analyses

These will also be analysed using GLMs with the treatment arm as the single predictor and country (Kenya, Malawi and Tanzania) and gravidity (pauci and multigravidae) as control variables. The point estimate of the treatment effects with 95% CI will be derived via specification of a GLM model for each secondary outcome depending on its distribution. For a binary outcome such as the components of primary endpoint, similar analysis to the primary endpoint analysis will be performed and the treatment effects measured as RR will be generated. For a continuous outcome like birthweight, a Gaussian distribution will be assumed and identity link function will be used. Correspondingly the mean difference and its 95%CI between two arms will be calculated. For a count outcome such as the number of SAEs, Poisson distribution and log link function will be used, from which incidence rate ratio (IRR) and its 95% CI will be computed.

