#### 10.2.1.1 Adverse Event (AE)

Any untoward medical occurrence in a patient or clinical trial subject administered a medicinal product and which does not necessarily have a causal relationship with this treatment.

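### The booking and monthly recall instructions let pre-dose illness into the adverse-event record and let the same non-serious illness be elicited repeatedly

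*Protocol*

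**What the plan says.** **Booking visit (Section 7.5.1.6).** "All participants will be asked about any symptoms or illnesses they have had in the last month, and any medication taken". On where the answers go: "These will be recorded in the adverse events section of the CRF". And then: "All AEs shall also be evaluated for seriousness and reported accordingly".

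**Interim monthly visits (Section 7.5.2.5).** "Participants will be asked about any symptoms or illnesses they have had since the start of pregnancy". The same section sends the answers, with the medication history, to the CRFs in general. The AE section is not named here.

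**AE definition (Section 10.2.1.1).** "Any untoward medical occurrence in a patient or clinical trial subject administered a medicinal product", whether or not the treatment caused it.

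**AE capture.** The vomiting-questionnaire and AE row of Table 1 is blank at enrolment, is first marked at the initial IPTp course, and is marked again at visits 2 to 4, at delivery and at the postnatal visits. Footnote f to that table says: "Vomiting and other adverse events (AEs) occurring within 30 minutes of the first dose will be assessed". It leaves later AEs to passive surveillance. Section 10.2.2 says that women with adverse events from the study interventions or other treatments are identified at follow-up visits, and that mild events are noted in the CRF.

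**Use of the data.** Dizziness and gastrointestinal complaints are tolerance outcomes (Section 7.4.2.3), and other SAEs and AEs are a safety outcome (Section 7.4.2.2). On analysis, Section 9.3.2.2 says: "For a count outcome such as the number of SAEs, Poisson distribution and log link function will be used". Section 9.3.3 examines safety by number of DP courses received.

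**The concern.** The two recall windows look reversed. At booking, where everything recalled precedes the study drug, the window is one month and the answers are filed as adverse events. At follow-up, where one month is the natural interval, the window is the whole pregnancy. No reason is given for the difference.

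Two kinds of entry that do not belong in a comparison of randomised arms can follow. One is illness that began before randomisation, when the arms cannot differ by treatment. The other is the same illness reported again at successive visits. Pre-randomisation illness is expected to balance across arms, so counting it pulls a true excess of AEs on DP or DP+AZ towards the null, which is the unfavourable direction for a safety comparison. Repeats make counts within a woman dependent, so a plain Poisson model applied to them would understate the variance. In the analysis by number of courses, women with more courses also have more visits at which to re-report, which could mimic a dose-response.

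**Working it through.** The protocol states no AE rate or count, so there is no figure of its own to reproduce. The check sets the sections side by side and then gives two illustrations.

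**1. Booking visit against the AE definition.** Section 7.5.1.6 covers the month before booking. The first IPTp course is given at that visit or later (Sections 7.5.1.4 and 7.3.2.1.1), so the recalled month precedes any study drug. Section 10.2.1.1 ties an AE to a subject who has been given a medicinal product, and Table 1 starts AE capture at the first course. The three places do not agree. The safety population in Section 9.3.1.1 does not settle it, because it selects women who were dosed, not events with onset after dosing.

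**2. Monthly window against the schedule.** Enrolment is at 16 to 28 weeks (Section 7.2.1). A window from the start of pregnancy therefore always includes at least 16 weeks before randomisation and always contains the windows of all earlier visits.

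**3. How often one illness is asked about.** Section 7.3.1.1 gives 3 to 7 visits; call the number k and count booking as one.
- Illness in the month before booking: asked at booking and at k − 1 later visits, so k times, that is 3 to 7 (5 when k = 5).
- On-study illness with onset in the interval after visit j: asked at k − j visits. Averaged evenly over j = 1 to k − 1 this is k/2, that is 1.5 to 3.5 (2.5 when k = 5).

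These are maximum numbers of elicitations if nothing is de-duplicated. They are not AE counts.

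**4. Dilution if pre-dose events are counted.** Let b be the number of pre-dose events per control-arm on-study event, equal in both arms. Then

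apparent ratio = (true ratio + b) / (1 + b).

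The documents give no value for b; the range 0.1 to 2 is an assumption.

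| True ratio | b = 0.1 | b = 0.25 | b = 0.5 | b = 1 | b = 2 |
|---|---|---|---|---|---|
| 1.5 | 1.455 | 1.400 | 1.333 | 1.250 | 1.167 |
| 1.25 | 1.227 | 1.200 | 1.167 | 1.125 | 1.083 |
| 0.8 | 0.818 | 0.840 | 0.867 | 0.900 | 0.933 |

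For example, (1.5 + 0.1)/1.1 = 1.455 and (1.5 + 2)/3 = 1.167.

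**The case against.** The strongest reply is that the protocol never says the monthly answers become AEs. Section 7.5.2.5 sends them to the CRFs in general, whereas Section 7.5.1.6 names the AE section. Footnote f to Table 1 gives a separate route for later AEs. The only count outcome that Section 9.3.2.2 names is SAEs, and the SAE form records date of onset (Section 10.2.4), so SAEs can be placed before or after the first dose and counted once. Section 10.2.4.2 leaves common non-hospitalised illnesses out of aggregate reports unless they are at least possibly related. The SAP and the questionnaires, which are not shown, may restrict counts to events after the first dose and remove duplicates.

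Much of this stands. A reader might infer that AE counts will include pre-randomisation illness and will repeat each event monthly, even several-fold. For instance, take the average booking at 22 weeks (Section 6.2.3) and assume visits at 26, 30, 34 and 38 weeks. The recalled time is 26 + 30 + 34 + 38 = 128 weeks against 16 weeks after the first dose, a ratio of 8, with 4 × 22 = 88 weeks (69%) pre-dose. That is a ratio of recalled time, not of any AE count the protocol defines. It would carry over to counts only with a constant illness rate from conception, full re-reporting, every answer entered as an AE and no de-duplication. The documents do not support those assumptions.

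The reply does not remove the defect. It leaves the conflict between Sections 7.5.1.6 and 10.2.1.1 untouched. Section 10.2.2 makes follow-up visits a route for identifying AEs, alongside passive surveillance. The stated onset date covers SAEs only, while dizziness and gastrointestinal complaints are outcomes too. A SAP can restrict and de-duplicate non-serious events only if their onset was captured. Section 10.2.4.2 limits what is reported, not what is recorded.

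**Conclusion.** The point holds as a conflict in the collection rules. Section 7.5.1.6 contradicts the protocol's own AE definition and Table 1. Section 7.5.2.5 sets a window that reaches before randomisation and overlaps every earlier visit. Following the text as written can place pre-dose illness in the AE record and elicit the same non-serious illness more than once.

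Whether AE counts would be affected, and by how much, cannot be established from the protocol. The illustrative shrinkage of a true ratio of 1.5 to about 1.45 to 1.17 rests on the assumed range for b, on balance of pre-dose illness across arms, and on such events being kept in the count. The distortion of the analysis by number of courses is likewise a possibility, not a demonstrated effect.

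The primary endpoint is not affected. QTc, congenital malformations, maternal mortality and vomiting observed after the first dose do not depend on this recall question. The correction should be made because it concerns safety and tolerance outcomes and is close to free.

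**What to change.** - **Section 7.5.1.6:** record symptoms reported at booking as baseline or medical history, not in the AE section of the CRF, in line with Section 10.2.1.1 and Table 1.
- **Section 7.5.2.5:** start the recall window at the last study visit instead of the beginning of pregnancy, and record an onset date for each symptom or illness, non-serious ones included. Say whether the answers feed the AE record, so that this section, Section 10.2.2 and footnote f to Table 1 agree.
- **Counting:** with onset dates in hand, AE and tolerance counts, including those in the analysis by number of courses, take each event with onset after the first study dose once.

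The cost is a wording amendment and a small change to the CRF and its instructions. No extra participants or visits are needed, and the monthly recall question becomes shorter.

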### **7.5.3 Unscheduled visits during pregnancy**

Participants will be encouraged to visit the clinic if they feel unwell between scheduled appointments. Participants who present between appointments will be examined by study staff. Presenting symptoms, axillary temperature and blood pressure will be recorded. A finger-prick blood sample will be taken for Hb measurement (if clinically indicated) and malaria RDT for point of care, and a malaria smear and dried blood spot for later analysis of malaria. Any illness will be treated as appropriate and according to standard local care. The date of attendance, diagnosis and treatment will be recorded on the CRF, and any adverse events reported according to standard procedures.

### **7.5.4 Delivery visit**

Women will be encouraged to deliver on the maternity wards of the participating clinics, in which case they will be assisted to delivery by regular clinic midwives, and a specially trained staff will visit them on the ward and perform relevant examinations shortly after delivery. Women who deliver at home will be identified using a network of community health workers such as health surveillance staff or village health volunteers/workers, and will be requested to report to the health facility within 48 hours, to collect, as far as possible, the same information.

#### **7.5.4.1 Biological sampling mother**

A similar venous (up to 10 mL) or finger prick whole blood sample (~250 µL) will be taken as for the scheduled follow-up visits for the same assays as described in Table 1: Summary Table of Study Design and Schedule of Assessment, page 15 and in more detail in Appendix VII. Description of other clinical and laboratory methods, page 84. Women taking part in the component that assesses the impact on the carriage rate of macrolide resistant *Streptococcus* will be asked to provide another nasopharyngeal swab (if the delivery timepoint is missed this can be taken at subsequent post-natal follow-up visits up to 6-8 weeks post-partum).

#### **7.5.4.2 Placental sampling**

A blood sample will be collected from the delivered placenta by making an incision on the maternal side and collecting the pooled blood. This sample will be tested for malaria using standard microscopy of blood smear and PCR, and drug levels.

A 2cm x 2cm x 1cm specimen of placental tissue will be taken from the maternal side for histopathology testing for current and past malarial infection. An amnion roll will be included in the collection of the placental sample for histological evaluation of chorio and/ or amnionitis.

#### **7.5.4.3 Umbilical cord sampling**

A 5 mL umbilical cord blood sample will be taken for haemoglobin level, malaria molecular diagnostics, antibody and cell mediated immune responses to malaria and other pathogens, and nutritional biomarkers including leptin, adiponectin, and drug levels. This will be a total of 7 mL for those contributing to the assessment of the impact on immunological outcomes: Maternal antibody, trans-placental antibody transfer and multi-pathogen neonatal cell mediated immune responses (page 88) for the additional assays on cell mediated immune responses involving peripheral blood mononuclear cell (PBMC).

#### **7.5.4.4 Examination of the baby**

All babies shall be examined for vital status, jaundice and the presence of congenital abnormalities. Birthweight, using digital scales, head circumference, length, and umbilical abdominal circumference shall be measured. In a subgroup, additional new-born anthropometric measurements including body composition, chest circumference, abdominal circumference below the xiphoid process, mid-upper arm circumference, skinfold (triceps, biceps, subscapular, quadriceps) measures will be taken.

### **7.5.5 Postnatal visits**

#### **7.5.5.1 Seven-day postnatal visit**

Participants and their babies will be seen at the clinic by a study nurse around seven days after birth. The baby will be examined for the presence of jaundice and for any congenital anomalies that may have been missed at delivery. A heelprick sample (about 500 microL) will be taken in all babies with fever or other symptoms will have blood samples taken for testing by RDT, microscopy and DBS, and in a subgroup of asymptomatic babies for assays to assess immune responses to malaria and other infectious diseases. All treatment will be provided based on the RDT results. Standard postnatal advice and healthcare will be provided as needed for mother and baby, and any treatment and clinical findings for the baby recorded on the CRF.

Routine postnatal care will be provided for the women. In a sub-group of women, nutritional status postpartum shall be assessed through measurement of skinfold thickness, hip circumference, waist circumference and bioelectrical impedance analysis. Women who do not attend for this appointment will be visited at home if possible. Any infant deaths occurring before the visit will be recorded; the date and probable cause of death will be ascertained by verbal autopsy.

#### **7.5.5.2 Six to eight -week postnatal visit**

Participants and their babies will be seen again at the clinic around six to eight weeks after birth, at their baby's second vaccination visit. The baby will be examined for the presence of congenital anomalies that may have been missed at delivery or the first visit.

A similar heel prick sample (about 500 microL) as on day 7 will be taken again for malaria diagnosis and for immunological assays with treatment provided based on the RDT results. Standard postnatal advice and healthcare will be provided as needed for mother and baby, and any treatment and clinical findings for the baby recorded on the CRF. Routine postnatal care will be provided for the women. In a sub-group of women, nutritional status postpartum shall be assessed through measurement of skinfold thickness, hip circumference, waist circumference and bioelectrical impedance analysis. Women who do not attend the scheduled appointment will be visited at home

if possible. Any infant deaths occurring before the visit will be recorded; the date and probable cause of death will be ascertained by verbal autopsy.

A stool sample from the neonate will be collected to determine the gut microbiota. If not available on the day of visit, the mother shall be requested to submit the sample the following day. More detailed maternal and neonatal anthropometric measurements shall also be collected in a subgroup of approximately 1,464 children.

